### Sample Size

The calculation was performed with α=.05, a statistical power of 0.8 (80%), and an effect size of 0.8, resulting in a total sample size of 20. The target sample size includes a margin to accommodate potential dropouts. However, if the number of dropouts significantly impacts statistical power or data integrity, we plan to recruit additional participants to maintain the robustness of the analysis.

The sample size will be estimated using data from the 6-minute walk distance (6MWD), as sufficient effect size data for this outcome are available in the literature, and it is a widely recognized measure of functional walking capacity in rehabilitation research. However, performing the full 6MWD may be overly demanding for patients in the early postoperative period following limb amputation; therefore, the 2-minute walk distance (2MWD) will be selected as the primary end point. The 2MWD has been validated as a reliable and less physically demanding alternative to the 6MWD, with strong correlations reported between the two measures in neuromuscular and rehabilitation populations [13,15].

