**Results:**

The planned sample size is 20 patients, calculated using JMP version 12 (SAS Institute) based on an expected 1.5-fold improvement in 6-minute walk distance (effect size 0.8, α=.05, power=0.8). Analyses will be performed using SPSS version 15.0 (IBM Corp). The 2-minute walk test (primary outcome) and secondary outcomes will be compared at baseline, post intervention, and 6-month follow-up using 1-way analysis of variance or Kruskal-Wallis test, and *P* values <.05 and 95% CIs will be reported.

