### Statistical Analysis

The target sample size was set at 20 patients scheduled for lower limb amputation. Using JMP version 12 (SAS Institute), the sample size was calculated based on a research design assuming that the 6MWD would improve by a factor of 1.5, referencing previous studies on gait analysis using the HAL [16]. The calculation was performed with α=.05, power=0.80, and a prespecified effect size.

The primary analysis population for efficacy evaluation will be the Full Analysis Set (FAS), whereas the secondary analysis population will be the Per Protocol Set (PPS).

The FAS includes all study participants who have undergone at least one session of HAL-assisted gait training and have had at least one efficacy-related observation thereafter. However, individuals who fail to meet the eligibility criteria will be excluded. The PPS comprises participants from the FAS who have completed HAL-assisted gait training (5 days per week, 30 minutes per day) without major deviations from the study protocol and for whom the primary evaluation item can be assessed.

Statistical analyses will be conducted using SPSS version 30.0 (IBM Corp). The primary evaluation item, the 2-minute walking distance, will be analyzed using the FAS population, and the mean (SD) [or median (minimum-maximum)] will be calculated. Comparisons between preoperative, postintervention, and 6-month postoperative outcomes will be performed using a 1-way ANOVA or the Kruskal-Wallis test, with a 2-sided significance level of 5%, and a 95% CI will be calculated. In addition, the same analysis will be performed using the PPS as a secondary approach.

For secondary evaluation items, analysis will also be conducted using the FAS population. The mean (SD) [or median (minimum-maximum)] will be calculated for bilateral lower limb muscle strength, skeletal muscle mass, sensory impairment, range of motion, Berg Balance Scale, timed up and go test, gait parameters (step length, stride length, weight distribution, and gait speed during the 10-minute walk test), maximal oxygen uptake, and Locomo 25. Comparisons between preoperative, postintervention, and 6-month postoperative outcomes will be performed using a 1-way ANOVA or the Kruskal-Wallis test, and multiple comparisons will be conducted using the Tukey method (or Steel-Dwass test). A 2-sided significance level of 5% and a 95% CI will be used. The same analysis will also be performed using the PPS as a secondary approach.

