### Comparison With Prior Work

Early neurorehabilitation may facilitate the smooth acquisition of walking patterns. Previous studies on HAL-assisted gait training in patients with cerebrovascular disease have shown that repetitive, precise walking movements help maintain and improve muscle strength and balance ability [16,17]. In addition, early initiation of prosthetic gait training has been reported to enable independent walking even in older women [18]. Thus, implementing early gait training may promote recovery of physical function within the first 8 weeks of postoperative rehabilitation. Furthermore, studies have shown that patients who used a training prosthesis during rehabilitation had shorter hospital stays compared with those who did not [19,20].

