### Limitations

A key limitation of this study is the absence of a control group, which restricts the ability to attribute observed improvements directly to HAL-assisted rehabilitation. Moreover, the absence of a conventional rehabilitation control group limits the ability to attribute improvements solely to the HAL intervention. The single-arm design is appropriate for an exploratory investigation; however, future randomized controlled trials will be necessary to confirm efficacy and compare HAL-assisted rehabilitation with conventional rehabilitation protocols.

Second, the sample size is limited to 20 participants. This decision reflects the exploratory nature of the study and anticipates substantial individual variability in residual limb characteristics and rehabilitation backgrounds among transfemoral amputees. Third, the application of HAL is subject to technical constraints related to patient physique and residual limb condition, meaning it cannot currently be applied to all individuals with lower limb amputations. These limitations, arising from narrow eligibility criteria (eg, height, weight, and residual limb conditions), may restrict the generalizability of the findings. However, such strict criteria are necessary to ensure the safe and effective use of the HAL system, which requires specific physical and anatomical conditions for proper fitting and functionality. As the technology evolves, future studies may consider broader inclusion criteria to enhance applicability to the wider amputee population. Ultimately, this research will contribute to the development of guidelines for early rehabilitation following lower limb amputation and facilitate multicenter collaborative studies to strengthen the evidence base.

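### The stated 80% power is derived for the 6-minute walk, which the article does not list as an outcome, so it is unsupported for the 2-minute walk, the primary endpoint

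*Protocol article*

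**What the plan says.** Four places give a basis for the sample size: the Results paragraph of the abstract, Methods (Sample Size), Methods (Statistical Analysis) and Results (Sample Size and Participant Flow).

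- Sample Size gives the inputs: "The calculation was performed with α=.05, a statistical power of 0.8 (80%), and an effect size of 0.8". The number it arrives at is 20 patients. It names the source outcome: "The sample size will be estimated using data from the 6-minute walk distance (6MWD), as sufficient effect size data for this outcome are available".
- Statistical Analysis gives the assumed gain, "assuming that the 6MWD would improve by a factor of 1.5, referencing previous studies on gait analysis using the HAL", and refers to a prespecified effect size without repeating its value. The abstract and the Results section give the 1.5-fold 6MWD gain together with 0.8.
- Sample Size then makes 2MWD the primary endpoint, because the longer test may be too demanding soon after amputation. It says the two tests correlate strongly in neuromuscular and rehabilitation populations.

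Table 1 lists the 2-minute walk, the TUG and the 10-m walk, but no 6-minute walk. The analysis lists in Statistical Analysis do not contain it either. No expected 2MWD change, SD, effect size or correlation coefficient is given. The planned test for 2MWD is a 1-way ANOVA or Kruskal-Wallis test over three time points at a two-sided 5% level.

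Limitations explains the size of 20 by the exploratory nature of the study and adds that the decision "anticipates substantial individual variability in residual limb characteristics and rehabilitation backgrounds".

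**The concern.** Power belongs to a particular endpoint and a particular test. Here it was worked out for one endpoint and is presented as the power of a trial that tests another. The link offered is a correlation, which describes how patients rank on two tests. The quantity needed for power is the mean change divided by the SD of the change on 2MWD, and a correlation between tests supplies neither term.

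At stake is how the primary result is read. The 80% figure stands without qualification in the abstract, Methods and Results. A reader meeting a non-significant 2MWD result could use it to judge how much that result rules out, although the document gives no basis for doing so.

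A smaller point belongs with this one. Expected heterogeneity among patients is offered as part of the reason for limiting the trial to 20. If that heterogeneity carries into the change in 2MWD, it enlarges the SD, shrinks the standardised effect and lowers power. It argues for more patients, not fewer.

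**Working it through.** **Inputs from the article.** Alpha 0.05, two-sided (Statistical Analysis); power 0.80; effect size 0.8, type not stated; N = 20, single arm; assumed 6MWD gain 1.5-fold. No mean, SD or SD of change is given for either walk test, and no dropout rate.

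**Step 1: the plan's own figure.** For a single-arm comparison of two time points the natural calculation is a paired t-test. Its power is that of a noncentral t with n − 1 degrees of freedom and noncentrality d·√n, where d = mean change / SD of change. With d = 0.8:

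- n = 14: power 79.0%
- n = 15: power 82.1%, so 15 is the required number
- n = 20: power 92.4%

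The 20 is therefore not reproduced from the stated inputs by a paired test. It would follow from 15/(1 − 0.25) = 20, but no 25% dropout rate is stated. The test behind the figure of 20 is thus also unknown.

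**Step 2: does the 1.5-fold gain fix the 0.8?** With baseline mean 1, the mean change is 0.5. With baseline coefficient of variation CV and pre-post correlation r, the SD of change is CV·√(2 − 2r) if the SD stays constant, or CV·√(1 + 1.5² − 2·1.5·r) if it grows with the mean. Over assumed ranges of CV 0.3 to 1.0 and r 0.3 to 0.9:

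- largest d: 0.5/(0.3·√0.2) = 3.73
- smallest d: 0.5/(1.0·√2.35) = 0.33

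So 0.8 is one value among many that fit a 1.5-fold gain, even for 6MWD. For 2MWD neither the fold gain nor the SD is given.

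**Step 3: what 20 patients deliver on 2MWD.** This needs no 6MWD input, only a named test. Assuming a paired two-sided 5% t-test of week 8 with preoperative, solve for the d that gives 80% power:

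| Evaluable patients | Standardised 2MWD change for 80% power |
|---|---|
| 20 | 0.66 |
| 18 | 0.70 |
| 16 | 0.75 |

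The half-width of the 95% CI for the mean change with 20 patients is t(0.975; 19)/√20 = 2.093/4.472 = 0.47 SD of the change.

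**Step 4: dependence on the unknown effect.** With 20 evaluable patients and the same test, assumed values of d give power 92% at 0.80, 86% at 0.72, 78% at 0.64, 72% at 0.60 and 53% at 0.48. The documents do not say where 2MWD lies in this range.

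**Step 5: dependence on the test.** Take the planned 1-way ANOVA literally, as three independent groups of 20, with assumed means 0, 0.8 and 0.8 in units of the within-time-point SD. Then Cohen's f = 0.8·√2/3 = 0.377, the noncentrality is 60·0.377² = 8.53, and power is about 72%. The 0.8 here is scaled by a different SD from the one in the paired test, so 72% and 92% are not two estimates of one quantity. They show that a power statement has no meaning until the test and the type of effect size are named.

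**The case against.** The best defence is that nothing is hidden. The article says openly that 6MWD is a proxy, explains why the longer test is unsuitable early after surgery, cites a validation of the shorter one, and calls the study exploratory, with randomised trials needed to confirm efficacy. All of that stands, and it makes this a matter of wording. It does not repair the inference, because the justification given for the proxy does not do what is asked of it.

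Stronger readings are tempting and do not hold:

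- A reader might infer that the trial is underpowered. The documents do not show this. In a paired test 20 evaluable patients keep 80% power down to d = 0.66, and the 2MWD effect could be larger or smaller than the 6MWD one.
- A reader might shrink 0.8 by a plausible correlation to obtain a 2MWD effect. That treats the correlation as carrying the effect over, which is the step in dispute.
- A reader might divide the 50% gain by 0.8 to recover an SD of change and then try smaller gains. That assumes 0.8 is a paired effect size derived from the 1.5-fold gain, which the article never says.

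On variability, the Limitations sentence concerns residual limbs and rehabilitation backgrounds, not the SD of 2MWD change. That is fair, so the criticism is only that such heterogeneity is no reason for a small sample.

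It is also fair that the paired figures are for a test the article does not name. They illustrate the form of the statement needed and cannot simply be pasted beside the present analysis text.

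**Conclusion.** The concern holds in limited form. The 80% power is derived from 6MWD, which appears in neither the outcome table nor the analysis lists of the article. The correlation cited cannot transfer the effect size, so 80% power for 2MWD is unsupported. It is not shown to be too low.

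As to size, under a paired two-sided 5% t-test, 20 evaluable patients give 80% power only if the standardised 2MWD change is at least 0.66. That threshold rises to 0.75 with 16. These figures rest on the assumed paired test and on approximately normal changes. The absence of 6MWD is judged from the article alone, as the full protocol and any SAP are not shown.

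**What to change.** Change wording in five places.

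1. In the abstract's Results, Sample Size, Statistical Analysis, and Sample Size and Participant Flow, say that the effect size of 0.8 is a 6MWD proxy, and do not present 80% as the power for 2MWD.
2. There, state what 20 patients deliver on 2MWD and name the test. For a paired two-sided 5% comparison of week 8 with preoperative, that would be a detectable standardised change of 0.66, 0.70 or 0.75 at 80% power with 20, 18 or 16 evaluable patients, and a 95% CI half-width of about 0.47 SD of the change with 20. Because the analysis text names 1-way ANOVA or Kruskal-Wallis, the power statement and the analysis must be made to match before either figure is used.
3. Either cite a 2MWD effect size with its source, or say that none was used.
4. In Limitations, remove expected variability as a reason for limiting the sample to 20 and rely on the exploratory nature of the study, which is already given there.

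This needs no extra patients, visits or measurements. The cost is that the stated power claim becomes less favourable.

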### Statistical Analysis

The target sample size was set at 20 patients scheduled for lower limb amputation. Using JMP version 12 (SAS Institute), the sample size was calculated based on a research design assuming that the 6MWD would improve by a factor of 1.5, referencing previous studies on gait analysis using the HAL [16]. The calculation was performed with α=.05, power=0.80, and a prespecified effect size.

The primary analysis population for efficacy evaluation will be the Full Analysis Set (FAS), whereas the secondary analysis population will be the Per Protocol Set (PPS).

The FAS includes all study participants who have undergone at least one session of HAL-assisted gait training and have had at least one efficacy-related observation thereafter. However, individuals who fail to meet the eligibility criteria will be excluded. The PPS comprises participants from the FAS who have completed HAL-assisted gait training (5 days per week, 30 minutes per day) without major deviations from the study protocol and for whom the primary evaluation item can be assessed.

Statistical analyses will be conducted using SPSS version 30.0 (IBM Corp). The primary evaluation item, the 2-minute walking distance, will be analyzed using the FAS population, and the mean (SD) [or median (minimum-maximum)] will be calculated. Comparisons between preoperative, postintervention, and 6-month postoperative outcomes will be performed using a 1-way ANOVA or the Kruskal-Wallis test, with a 2-sided significance level of 5%, and a 95% CI will be calculated. In addition, the same analysis will be performed using the PPS as a secondary approach.

For secondary evaluation items, analysis will also be conducted using the FAS population. The mean (SD) [or median (minimum-maximum)] will be calculated for bilateral lower limb muscle strength, skeletal muscle mass, sensory impairment, range of motion, Berg Balance Scale, timed up and go test, gait parameters (step length, stride length, weight distribution, and gait speed during the 10-minute walk test), maximal oxygen uptake, and Locomo 25. Comparisons between preoperative, postintervention, and 6-month postoperative outcomes will be performed using a 1-way ANOVA or the Kruskal-Wallis test, and multiple comparisons will be conducted using the Tukey method (or Steel-Dwass test). A 2-sided significance level of 5% and a 95% CI will be used. The same analysis will also be performed using the PPS as a secondary approach.

Furthermore, for Barthel Index (BI), Functional Independence Measure (FIM), Frenchay Activities Index (FAI), SF-36, Health Utilities Index, EQ-5D-5L (quality-adjusted life years), long-term care insurance certification level, General Self-Efficacy Scale, and WHODAS 2.0, the mean (SD) [or median (IQR)] will be calculated. Comparisons between preoperative, postintervention, and 6-month postoperative outcomes will be performed using a 1-way ANOVA or the Kruskal-Wallis test, with multiple comparisons conducted using the Tukey method (or Steel-Dwass test). A 2-sided significance level of 5% and a 95% CI will be calculated. The same analysis will be conducted using the PPS as a secondary approach.

The primary efficacy analysis will be conducted using the FAS, which includes all participants who received at least one session of HAL-assisted gait training and have at least one postintervention efficacy observation. Participants who are found to violate key eligibility criteria will be excluded from the FAS.

A secondary analysis will be performed using the PPS, which is a subset of the FAS consisting of participants who completed HAL training (5 days per week, 30 minutes per session) without any major protocol deviations and for whom the primary outcome data are available.

For missing data, a descriptive analysis will first be conducted to assess the pattern and mechanism of missingness. If the data are judged to be missing at random, multiple imputation using chained equations will be applied to handle missing values in the primary outcomes. Additionally, sensitivity analyses will be performed by comparing results between complete-case and imputed datasets to evaluate the robustness of the findings.

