As the residual limb matures, prosthetic gait training will begin using a temporary prosthesis. Patients who underwent transfemoral amputations will use a transfemoral prosthesis, whereas those who underwent transtibial amputations will use a transtibial prosthesis. The temporary prosthesis is standardized for gait training and will not differ among patients, whereas the socket will be custom-made to fit the residual limb of each patient. HAL-assisted gait training will continue until postoperative week 8. The hospitalization period will last until the completion of the evaluation at postoperative week 8. At this point, all assessment items will be measured, with a final evaluation conducted 6 months postoperatively.

During gait training, patients may experience significant fatigue, inflammation at the electrode site, abrasions at contact points between the HAL and the body, and adverse muscle or joint pain. If any of these occur, training will be immediately discontinued, and the patient will undergo a medical examination.

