**Figure 2 figure2:**
[figure not shown]
Flowchart for trial. HAL: Hybrid Assistive Limb (developed by Japan's Tsukuba University and the robotics company Cyberdyne).

According to the study protocol, criteria for discontinuing or modifying the allocated intervention for individual participants include the following: withdrawal of informed consent; discovery after enrollment that the participant does not meet the eligibility criteria; worsening of the primary disease that makes use of the study device inappropriate; exacerbation of comorbid conditions that hinders continuation; occurrence of adverse events that make continuation difficult; confirmation of pregnancy; significant noncompliance with study procedures; markedly low frequency of intervention use due to postoperative complications; premature termination of the entire study; or any other reason deemed appropriate by the investigator (YM, KU, and TA).

When discontinuation occurs, the reason will be explained to the participant if necessary, and postdiscontinuation care will be provided to ensure the participant is not disadvantaged.

The principal investigator (YM) considers early termination of the study in cases where the planned number of participants cannot be recruited within the designated period; the ethical review board requires protocol changes that are not acceptable; facts or information are discovered that undermine the ethical or scientific validity of the study; the integrity of the study conduct or results is compromised; or critical information emerges regarding the quality, safety, or effectiveness of the study device.

If the ethics committee recommends or instructs discontinuation, the study will be terminated accordingly. In such cases, the reason for termination will be reported in writing to the hospital director, and a study termination report will be submitted without delay. Notification will also be made to the ethics committee and the Ministry of Health, Labour and Welfare within 10 days of termination.

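### The full analysis set requires an efficacy value after HAL training, so a patient lost early with complications can leave every efficacy analysis and raise the week-8 walking distance

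*Protocol article*

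**What the plan says.** All places are in the Methods of the protocol article.

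- **Analysis sets (Statistical Analysis).** The FAS holds patients who "have undergone at least one session of HAL-assisted gait training and have had at least one efficacy-related observation thereafter", less those found ineligible. Later in the same section the condition is restated: patients must "have at least one postintervention efficacy observation". The per-protocol set (PPS) is a subset of the FAS.
- **Schedule (Outcomes, Table 2).** Physical function, activities and participation are ticked at preobservation, 8 weeks and 6 months. The withdrawal column carries adverse event monitoring alone. The Outcomes text also mentions gait evaluations at 2 weeks, which Table 2 does not tick.
- **Exposure (Interventions).** At least one HAL session takes place before surgery.
- **Stopping (Interventions).** The article lists "criteria for discontinuing or modifying the allocated intervention for individual participants", among them "markedly low frequency of intervention use due to postoperative complications".
- **Hospital stay (Interventions).** "The hospitalization period will last until the completion of the evaluation at postoperative week 8".
- **Missing data (Statistical Analysis).** The pattern and mechanism are described first. If the data are judged missing at random, "multiple imputation using chained equations will be applied to handle missing values in the primary outcomes". The sensitivity check consists of "comparing results between complete-case and imputed datasets".

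**The concern.** Membership of the primary set depends on having an outcome value after training starts. Because the first session is preoperative, a patient meets the exposure condition before any surgical complication can occur. If that patient's stump then fails to heal, HAL is stopped and the patient leaves without another assessment, the rule removes the patient from the FAS and hence from the PPS.

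Such a patient would probably have walked less at week 8 than those who stayed. Removing the patient, or imputing a value that ignores why it is missing, can move the week-8 2MWD upward, in the direction of the study hypothesis. A single-arm trial has no comparison arm in which similar losses might offset this.

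The planned checks would not show it. FAS against PPS cannot, because the patient is in neither. Complete-case against imputed data cannot, for a patient who was never in the set. For a patient kept in the FAS without a week-8 value, agreement between the two analyses does not rule out loss that depends on the unseen outcome.

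**Working it through.** **Following one patient through the rules.** The patient had preoperative HAL and the amputation, then stopped HAL for complications.

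1. Still measured at week 8: in the FAS with an observed value. No bias arises.
2. Leaves before week 8, with no later efficacy value: outside the FAS and the PPS.
3. Misses week 8 but returns at month 6: in the FAS with the week-8 value missing, and imputed if the data are judged missing at random.
4. Leaves after a 2-week gait evaluation: depends on whether that evaluation takes place (the text and Table 2 differ) and whether it counts as an efficacy observation. If so, as route 3; if not, as route 2.

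No sentence says that assessment continues once HAL stops, so the choice between route 1 and the others is not fixed.

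**Size.** The article gives no loss rate and no expected distance for lost patients, so there is no stated figure to reproduce. The planned 20 serves only as the denominator. Everything else below is an assumption.

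Let f = k/20 be the share lost, r the lost patients' true week-8 mean divided by that of the kept patients, and v the value used for them on the same scale. Exclusion gives the same mean as v = 1.

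Overstatement of the week-8 mean = [(1 − f) + f·v] / [(1 − f) + f·r] − 1

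| Lost of 20 | Excluded or imputed at kept mean; truth 0 m | Excluded or imputed at kept mean; truth half the kept mean | Imputed at half the kept mean; truth 0 m |
|---|---|---|---|
| 0 | 0 | 0 | 0 |
| 1 | 1/0.95 − 1 = 5.3% | 1/0.975 − 1 = 2.6% | 0.975/0.95 − 1 = 2.6% |
| 2 | 1/0.90 − 1 = 11.1% | 1/0.95 − 1 = 5.3% | 0.95/0.90 − 1 = 5.6% |
| 4 | 1/0.80 − 1 = 25.0% | 1/0.90 − 1 = 11.1% | 0.90/0.80 − 1 = 12.5% |

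**The change from baseline.** The planned analysis compares three time points: "Comparisons between preoperative, postintervention, and 6-month postoperative outcomes will be performed using a 1-way ANOVA". Exclusion also removes the patient's preoperative value. With q the lost patients' preoperative mean relative to the kept patients' mean, exclusion overstates the ratio of week-8 to preoperative means by

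[(1 − f) + f·q] / [(1 − f) + f·r] − 1

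For 2 of 20 lost with r = 0:
- q = 1: 1/0.90 − 1 = 11.1%
- q = 0.5: 0.95/0.90 − 1 = 5.6%

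If q = r the ratio is unbiased, and if q is below r the error runs the other way. This offset applies to exclusion, not to imputation, where the preoperative value stays in.

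**Imputation.** A large simulation took wound course to correlate 0.7 with week-8 2MWD, made the worst 10% to 30% by wound course missing, and imputed by regression on preoperative 2MWD alone. The complete-case mean was too high by 0.14 to 0.35 SD. After imputation the excess was:

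- 0.14 to 0.35 SD if preoperative and week-8 distance are uncorrelated;
- 0.11 to 0.28 SD at correlation 0.5;
- 0.08 to 0.20 SD at correlation 0.7.

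Under these assumptions imputation reduces the bias but does not remove it. An imputation model that used healing or exposure data could do better. The article does not describe its model, and that is detail an article may leave out.

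**The case against.** The strongest answer is that the situation is narrow and mostly handled. Patients must be able to comply with the hospital schedule to be eligible, they stay in hospital until the week-8 evaluation, and the stopping criteria concern the intervention rather than follow-up. The bias needs a patient who both stops HAL and leaves without a later assessment. This stands: it limits how often the problem can arise, and nothing in the article suggests that it will be common. It does not close the gap, because no sentence ties stopping HAL to continued assessment.

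Four stronger readings are tempting, and the article does not support them.

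- *Stopping HAL removes the patient from the analysis.* It does not. A patient off HAL who is measured at week 8 stays in the FAS.
- *Early leavers will be imputed as missing at random.* Imputation is conditional on that judgement, after the missingness has been examined. Loss through wound failure is a pattern that this step could flag.
- *The two FAS statements contradict each other.* The second wording can be read simply as after the first session, which is the same rule as the first. Only by importing the time-point label from the ANOVA sentence do they diverge. One definition would be cleaner, but this is a weak conflict.
- *The percentages estimate the trial's bias.* They do not. They rest on assumed losses and distances and describe the week-8 mean alone.

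The Limitations section says that the week-8 result directly reflects the effect of early HAL rehabilitation. In context that sentence contrasts week 8 with a less sensitive month-6 visit, and the missing control group is disclosed separately. Rewording it is not needed here, nor is reporting from session logs.

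**Conclusion.** The point holds in a limited form. The primary set is conditioned on a later efficacy value, no efficacy measure is scheduled at withdrawal, and a patient lost early after complications can disappear from every efficacy analysis or be imputed on an assumption that may not fit. Either can bias the week-8 2MWD upward, given the clinical assumption that such patients walk less than those who stay.

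The size cannot be determined from the article. It is zero if every patient is measured at week 8. For the pre-to-post change under exclusion it is smaller if leavers also walked less before surgery, and can vanish. In the table, an overstatement of at least 10% in the week-8 mean needs 2 of 20 lost at 0 m, or 4 of 20 at half the kept mean, with exclusion or imputation at the kept mean. Severity is minor to moderate: the scenario is narrow, but with 20 patients one or two such cases matter and the remedy is cheap.

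**What to change.** 1. Define the FAS once, as all eligible enrolled patients who had the amputation and at least one HAL session, without the later-observation condition.
2. State that stopping HAL does not end assessment, and that the 2MWD is measured at week 8 and month 6 regardless of HAL use.
3. Score 0 m when a patient is unable to walk at the visit.
4. Report the number lost, with a sensitivity result that sets lost patients to 0 m beside the multiple imputation. This is a deliberately unfavourable not-at-random case.
5. If extra patients are recruited to replace dropouts, as the Sample Size section allows, keep the lost patients in the analysis. Recruitment restores the number but does not undo the selection.
6. Reconcile the 2-week gait evaluation in the Outcomes text with Table 2.

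The cost is low, since both visits are already scheduled and patients are in hospital until week 8. The downside is zeros in the data, hence a lower mean and more skew, which favours a rank-based summary. The plan already allows medians and a rank test.
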